### Randomization and allocation

After the start of the research, all the patients admitted to the ICU will be assessed for inclusion based on the eligibility criteria through daily visits in direct communication with the multidisciplinary team. The patients that met the eligibility criteria will be allocated randomly in the intervention and control groups using the simple randomization strategy [14–16]. The numbers associated with the identities of the eligible patients will be concealed in an opaque, coded, and unidentified envelope [17], which will be signed and dated by the researcher responsible for the allocation. Only the physiotherapist who performed the intervention will know the meaning of the code contained in the envelope and, therefore, will know which patients received the progressive active mobilization protocol. Randomization will be performed by an independent researcher not involved in the study (the independent researcher will not be part of the intervention or the evaluation and will be blinded to the intervention and control codes).

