### Intervention outcomes

Socio-demographic, health, and lifestyle data will be collected from the patients through the report of the legal guardians and when possible, the patients themselves. Data of the medical aspects of the study will be collected through the patient's chart, ICU monitors, and direct communication with the multidisciplinary team. The data will be recorded in an appropriate form by properly trained researchers. Researchers who collected study data will not be part of the hospital staff.

All outcomes will be assessed according to the outcome assessment recommendations of Young et al. [25]. The primary outcome will be the length of stay in the ICU. The secondary outcome measures included:

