### Sample size calculations

The sample size calculation will be based on a mean difference in the length of hospital stay of 2.5 days; considering a confidence interval of 95%, power of 80%, and a ratio of 1: 1 between the two groups. Based on the averages of the study by Dong et al. [33] (12.7±4.1 vs 15.2±4.5 days), a sample size of 94 patients was obtained, 47 for each group. After adjusting 20% for missing, death, loss to follow-up, and withdrawals, the corrected sample was 118 subjects. The study by Dong et al. [33] was chosen because it had a population similar to that in the present study. Among other aspects of population similarity, the study involved patients able to perform activities independently and with a probability of <50% for death at 6 months. The sample size calculation will be performed using the module that calculates sample sizes to compare two averages available on the website: https://www.openepi.com/SampleSize/SSMean.htm.

This sample also will be sufficient to contemplate the functional independence objective, based on the percentage of patients returning to their functional state at the time of hospital discharge (FSS = 35). A final sample size of 86 patients was obtained, 43 for each group, based on 50% of patients returning to the previous functional state at the time of hospital discharge [34] and assuming that 80% of the patients remained in the intervention group at the time of hospital discharge.

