### Data analysis

For the analysis of demographic and clinical data, descriptive statistics will be used. The data of continuous variables will be analyzed with measures of central tendency and dispersion. The categorical variable data will be analyzed with frequency measurements. To perform the inferential statistics, tests for normality and homogeneity of variance will be performed. Since the data will be normally distributed, analysis of variance (ANOVA) will be used to compare the mean differences of the variables, followed by the Bonferroni post hoc test. If there will be no normal distribution, the Kruskal-Wallis test will be used, followed by the Mann-Whitney post-hoc test. χ2 tests will be used to evaluate the differences in the categorical variables between the groups.

Kaplan-Meier analysis will be used to estimate ICU LOS, mortality, and mechanical ventilation time, and a log-rank will be used to assess the difference between the groups. Poisson or negative binomial model will be used to estimate the incidence rate ratio. Stratified analyses will be performed according to age, initial functional status, and the Acute Physiology and Chronic Health Enquiry (APACHE-II) score to identify potential confounders. Cohen's *d* effect sizes will be also calculated. Before carrying out the analyzes, test methods assumptions will be verified.

Mean and median differences and 95% confidence intervals will calculated. The significance threshold will be used *P* < .05 for each outcome and testing will be used two-sided. The statistical software used will be used IBM SPSS for Windows 21.0. All study analyses will be used performed according to the intention to treat.

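### Age, initial functional status and APACHE-II serve only to look for confounders in stratified analyses; they should be covariates fixed in advance in one primary model for ICU stay

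*Protocol article*

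**What the plan says.** Under Intervention outcomes, the article states: "The primary outcome will be the length of stay in the ICU". Under Data analysis, the group comparisons are ANOVA or, without normality, Kruskal-Wallis for the variables in general, and Kaplan-Meier with a log-rank test for ICU stay by name. None of these is described as adjusted. A Poisson or negative binomial model is also planned for an incidence rate ratio, with neither its outcome nor any covariates named.

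The baseline factors then appear: "Stratified analyses will be performed according to age, initial functional status, and the Acute Physiology and Chronic Health Enquiry (APACHE-II) score". The purpose attached to that sentence is "score to identify potential confounders". No cut-points are given, nor what follows if a confounder is found.

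Under Randomization and allocation, eligible patients "will be allocated randomly in the intervention and control groups using the simple randomization strategy". No blocking or stratification is described.

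**The concern.** The stated purpose does not fit a randomised design. Baseline differences between the arms arise by chance, and whether a factor predicts ICU stay is best judged from prior knowledge. Looking for confounders in strata of this trial requires its outcome data and leads naturally to a later decision on what to adjust for.

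Two things are at stake. First, precision: if the three factors predict ICU stay, an unadjusted comparison leaves that variation in the estimate. Second, reporting: with no fixed adjusted model, several defensible results could be produced and the plan does not say which one counts. The design does not compensate, because simple randomization leaves the distribution of age, function and severity to chance.

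**Working it through.** **Inputs from Sample size calculations and Data analysis.** The difference is 2.5 days, from: "The sample size calculation will be based on a mean difference in the length of hospital stay of 2.5 days". The article labels it hospital stay although the primary outcome is ICU stay; it is used here as the planning figure for the primary outcome. Means, SDs and numbers: "12.7±4.1 vs 15.2±4.5 days), a sample size of 94 patients was obtained, 47 for each group". Error rates and ratio: "considering a confidence interval of 95%, power of 80%, and a ratio of 1: 1 between the two groups". Tests are two-sided at 0.05. Inflation is 20%, to 118 patients (59 per arm).

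**Step 1: reproduce the plan's figure.** Sum of variances: 4.1² + 4.5² = 37.06 (common SD √(37.06/2) = 4.305).

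n per arm = 37.06 × (1.960 + 0.842)² / 2.5² = 46.5, rounded up to 47, so 94 in total. Inflation: 94 / 0.80 = 117.5, rounded up to 118. Both figures match the article. The calculation is for an unadjusted comparison of two means.

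**Step 2: power with and without adjustment.** In a linear model, covariates that explain a share R² of the variance reduce the residual variance by the factor (1 − R²):

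SE = √(37.06 × (1 − R²) / n); power = Φ(2.5 / SE − 1.96).

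Example, n = 47 and R² = 0: SE = √(37.06 / 47) = 0.888; 2.5 / 0.888 = 2.815; Φ(0.855) = 80.4%.

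R² is not in the documents. The range below is an assumption.

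| Assumed R² | Power, 47 per arm | Power, 59 per arm |
|---|---|---|
| 0 (unadjusted) | 80.4% | 88.4% |
| 0.02 | 81.2% | 89.0% |
| 0.05 | 82.3% | 89.9% |
| 0.10 | 84.3% | 91.4% |
| 0.20 | 88.3% | 94.1% |
| 0.30 | 92.0% | 96.5% |

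The standard error shrinks by √(1 − R²): 1% at R² = 0.02 (√0.98 = 0.99) and 16% at R² = 0.30 (√0.70 = 0.84). Gains for a time-to-event or count model were not computed.

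**Step 3: chance imbalance under simple randomization.** For a continuous factor in SD units, the difference between arm means has standard error √(2/n): 0.206 at 47 per arm and 0.184 at 59. The chance of a difference of at least 0.3 SD in either direction is 2 × (1 − Φ(0.3/√(2/n))):

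- 47 per arm: 0.3 / 0.206 = 1.45, so about 15%.
- 59 per arm: 0.3 / 0.184 = 1.63, so about 10%.

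This is for one given factor, with arms of equal size. The 0.3 SD threshold is chosen for illustration.

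**The case against.** The strongest reply is that an unadjusted analysis of a randomised trial is not an error. It is valid, it matches the calculation behind the sample size, and it delivers the planned 80% power. Chance imbalance is already allowed for in its p-value and confidence interval. All of that stands.

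A reader might infer that adjusters will be picked from the observed strata and that type I error is therefore inflated. The article does not say so. It names the three factors in advance and states no rule for selecting among them or for replacing the unadjusted result. A simulation of 94 analysed patients, with R² of 0.10 to 0.30, shows only a worst case. The unadjusted test and the pre-fixed adjusted test each stayed near 5%. Always taking the better of those two gave about 7–8%, and the best of five adjustment sets about 8–10%. Nothing in the article proposes that practice, so these figures bound what the open wording permits and do not describe the plan.

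It is also fair to say that the gain may be small. The eligibility criteria narrow the range of severity and function (predicted mortality above 50% by APACHE II is excluded; prior Barthel index must be at least 70), which could lower R². At R² = 0.02 the gain is under one percentage point.

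Finally, covariate lists and cut-points are commonly left to a statistical analysis plan, and the unnamed covariates of the count model are not a finding. What remains is what the article does state: a purpose for the stratified analyses that is misplaced in a randomised trial, with no other role given to these factors in comparing ICU stay.

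**Conclusion.** The point holds as an improvement in efficiency and clarity. The primary comparison is neither invalid nor short of its planned power. The shortcomings are that precision is given up and that the choice of adjustment is left open.

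The size depends on an R² that the documents do not give. Over the assumed range, the gain at 47 per arm runs from under 1 to about 12 percentage points; at 59 per arm it runs from under 1 to about 8. These figures rest on the article's planning SDs and on a linear model for mean stay. For the log-rank or count analysis, the direction should be the same if the factors are prognostic, but the amount is unknown.

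**What to change.** - Name one primary regression model for ICU stay that can carry covariates. A log-rank test cannot take continuous age or APACHE-II. The negative binomial model already planned is one option; a proportional hazards model beside the Kaplan-Meier curves is another.
- Include age and APACHE-II as continuous covariates, and functional level at entry, all fixed before outcome data are examined.
- Report the unadjusted log-rank or mean comparison as a sensitivity analysis.
- Delete the clause that gives confounder-finding as the purpose of the stratified analyses. Label any stratified results as exploratory subgroup analyses, with arm-by-factor interaction tests.

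The cost is a change of wording in Data analysis. Age, APACHE-II and functional level are already needed to apply the eligibility criteria, so no new data are required, and the target of 118 can stay.

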## Abstract

The dose of progressive active mobilization is still uncertain. The purpose of this study is to identify if the addition of a protocol of progressive active mobilization with dose and training load control to usual care is effective in reducing the length of stay in intensive care unit (ICU) and the improvement of the functioning, incidence of ICU-acquired weakness (ICUAW), mechanical ventilation duration and mortality rate in patients hospitalized in ICU. It is Double-blind randomised clinical trial. The setting for this trial will be medical and surgical ICU of a university hospital. The study participants will be 118 patients aged> 18 years admitted to ICU for less than 72 hours. Participants will be randomized to either an experimental or control group. The experimental group will undertake addition of a protocol of progressive active mobilization with dose and training load control to usual care, while the control group will undertake only usual care. The primary outcome will be length of ICU stay. The secondary outcomes will be Cross-sectional area and muscle thickness of the rectus femoris and biceps brachii, Change in muscle strength from the baseline, Functional Status, incidence of ICUAW, Days with mechanical ventilation and Mortality. All statistical analyses will be conducted following intention-to-treat principles. It has a detailed description of the dose of exercise, was designed with the strictest methodological criteria. These characteristics allow to investigate with greater certainty the results progressive active mobilization in critical patients, allowing replication and future combinations in meta-analyzes.

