Cross-sectional area and muscle thickness of the rectus femoris and biceps brachii measured by ultrasound, using an 8-MHz 5.6-cm linear transducer array (PLM805, Toshiba Medical Systems, Crawley, UK) immediately after randomization and at intervals of 48 h for 28 days or till discharge from the ICU, whichever occurred earlier. For evaluation of the rectus femoris, the transducer will be placed perpendicular to the long axis of the thigh on its superior aspect, three-fifths of the distance from the anterior superior iliac spine to the superior patellar border [26]. Biceps brachii will be evaluated at the midline between origin and insertion [27]. The transducer will be positioned with slight pressure.Change in muscle strength will be evaluated immediately after randomization, after 3 days and at intervals of 7 days, up to the 28th day or till discharge from the ICU. Muscle strength will be measured using the following: (1) Medical Research Council sum-score (MRC) [28]; (2) handgrip, using a hydraulic dynamometer (Saehan Corporation SH5001, Korea), with the handle pressed for at least 6 seconds in three trials with a 1-min intervals; the highest value of manual grip strength in kilograms (Kgf) will be considered for the analysis [29]; (3) hand-held dynamometer of elbow flexion and knee extension (model 01163; Lafayette Instrument, Ind) [30]; and (4) five Sit to Stand Tests [31].Functional status at 28 days after randomization or discharge from ICU will be measured using the FSS [23], Surgical Optimal Mobilization Score (SOMS) [12], and timed up-and-go score [32].ICUAW will be determined by a score lower than 48 on the MRC sum-score, according to Vanpee et al. [28].Days with mechanical ventilation and mortality at 28 days after randomization or discharge from the ICU.

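### Fifteen secondary measures are each tested at P < .05 with no ranking, cross-outcome adjustment or supportive label, while the abstract words effectiveness jointly on several of them

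*Protocol article*

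**What the plan says.** All references are to the protocol article; no separate analysis plan is at hand.

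- **Primary outcome (Intervention outcomes).** There is one: "The primary outcome will be the length of stay in the ICU". The last paragraph of the Introduction likewise attaches the effectiveness question to ICU stay, and lists the other outcomes in a separate sentence as secondary.
- **Secondary outcomes (Intervention outcomes).** The list opens with "Cross-sectional area and muscle thickness of the rectus femoris and biceps brachii measured by ultrasound". It continues with five strength measures, beginning "1) Medical Research Council sum-score (MRC) [28]; (2) handgrip, using a hydraulic dynamometer", then three functional scores, ICU-acquired weakness, ventilation days and mortality.
- **Objective (Abstract).** The stated purpose is to find out whether the added protocol is "effective in reducing the length of stay in intensive care unit (ICU) and the improvement of the functioning, incidence of ICU-acquired weakness (ICUAW"), and the sentence goes on to ventilation duration and mortality.
- **Sample size calculations.** After sizing for length of stay, the section adds: "This sample also will be sufficient to contemplate the functional independence objective". A second sample size follows.
- **Decision threshold (Data analysis).** "The significance threshold will be used *P* < .05 for each outcome and testing will be used two-sided".
- **Multiplicity wording (Data analysis).** The only such wording is a Bonferroni post hoc step after analysis of variance. If data are not normal, Mann-Whitney post hoc tests replace it and no correction is stated.

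**The concern.** The threshold sentence gives every secondary measure the same standard as the primary outcome. Nothing makes the secondaries conditional on ICU stay, orders them or marks them as supportive. The Bonferroni step works within one variable, so it does not limit error across different outcomes.

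On its own, a nominal .05 for secondaries beside a single primary is common. What makes it matter here is the abstract, which puts four further domains into the same effectiveness question as ICU stay. Muscle size, strength and function are also each measured three to five ways. If ICU stay shows no difference and one of the 15 measures crosses .05, the abstract's objective gives the authors a basis for calling the protocol effective on that outcome. The abstract also says the results are meant for replication and meta-analysis, so a chance finding could travel.

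**Working it through.** **1. The plan's own figure.** The document states no error rate across outcomes. The figure that can be reproduced is the sample size for length of stay. Inputs are a difference of 2.5 days, SDs of 4.1 and 4.5, two-sided 5% and 80% power.

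- Mean variance = (4.1² + 4.5²)/2 = (16.81 + 20.25)/2 = 18.53.
- n per group = 2 × (1.960 + 0.842)² × 18.53 / 2.5² ≈ 46.5, rounded up to 47, so 94 in total.
- Allowing for 20% loss: 94/0.8 = 117.5, rounded up to 118.

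Both figures agree with the plan. The size therefore rests on one comparison at two-sided 5%, with no allowance for further confirmatory tests.

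**2. Counting the secondary measures (Intervention outcomes).**

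| Group | Measures | Count |
|---|---|---|
| Ultrasound | area and thickness, two muscles | 4 |
| Strength | MRC sum-score, handgrip, elbow flexion, knee extension, sit-to-stand | 5 |
| Function | FSS, SOMS, timed up-and-go | 3 |
| ICU-acquired weakness | MRC sum-score below 48 | 1 |
| Ventilation days | | 1 |
| Mortality | | 1 |
| **Total** | | **15** |

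**3. Chance of at least one false positive when the protocol has no effect.** Each measure is counted once.

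- Expected number of results with P < .05: 15 × 0.05 = 0.75, whatever the correlation.
- Independent tests, either direction: 1 − 0.95^15 = 0.537.
- Independent tests, benefit only (2.5% each): 1 − 0.975^15 = 0.316.
- Common correlation ρ, with c = 1.96 and U standard normal: 1 − E[{Φ((c − √ρ U)/√(1−ρ)) − Φ((−c − √ρ U)/√(1−ρ))}^15]. For benefit only, drop the second Φ term.

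| Assumed correlation | Either direction | False benefit only |
|---|---|---|
| 0 | 54% | 32% |
| 0.5 | 36% | 18% |
| 0.8 | 20% | 10% |
| 0.9 | 14% | 7% |

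**4. Sensitivity.**

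- *Block correlation.* Take ultrasound, strength with ICU-acquired weakness, and function as three blocks, with ventilation and mortality separate. Correlations of 0.5 within and 0.2 between blocks give 45%. Correlations of 0.8 within and 0.5 between give 30%. The benefit-only figures are 23% and 15%.
- *Overlap of two measures.* ICU-acquired weakness is a cut of the MRC score. Counting 14 independent tests gives 1 − 0.95^14 = 51%.
- *Six outcome groups only.* One test for each group named in the Introduction gives 1 − 0.95^6 = 26.5% if independent, 21% at correlation 0.5 and 11% at 0.9.

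**5. The two statements of the objective, side by side.** The Introduction asks about effectiveness on ICU stay and then lists secondaries. The abstract asks about effectiveness on ICU stay and four other domains together. The threshold sentence is neutral between them, so the document does not settle which outcomes may support an effectiveness claim.

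**The case against.** The strongest reply is that the outcomes are already ranked where it counts. One primary is named in the Abstract, the Introduction and the Intervention outcomes section, and the Introduction ties effectiveness to it alone. A significance threshold is not a rule for trial success. Which secondaries are key or exploratory is often left to an analysis plan, and this article already promises differences, 95% confidence intervals and Cohen's d. Much of this stands, and it limits the point to secondary claims. It does not remove it: the article does not stay silent but states a threshold for each outcome, and the abstract contradicts the narrower objective.

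Some stronger readings are tempting but not supported:

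- *That the trial has a one-in-three chance of a false claim of effectiveness.* About one third is the either-direction figure at a correlation of roughly 0.5 to 0.6, which is an assumption, and it counts false harm. At 0.5 the false-benefit figure is 18%. The document also never says that a significant secondary makes the trial positive.
- *That repeated scans inflate the error further.* Ultrasound is done "immediately after randomization and at intervals of 48 h for 28 days or till discharge from the ICU", but no separate test at each scan is planned. With only two groups, the Bonferroni step may well be meant for time points. Scanning also stops at ICU discharge, so 15 scans would need a 28-day stay.
- *That the functional objective is a second confirmatory endpoint.* The sample size section presents it as a check that the sample is also adequate for that objective.

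**Conclusion.** The point holds for the secondary outcomes. The article states a per-outcome threshold of .05, lists 15 secondary measures without ranking, adjustment or label, and words the objective in two incompatible ways. The single primary outcome keeps its own 5% error as far as the secondaries are concerned.

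Under no effect, the chance of at least one secondary P < .05 runs from 54% (independent) to 14% (correlation 0.9), and that of a false benefit from 32% to 7%. Against the nominal 5% and 2.5%, even the lowest figures are nearly three times too high. The calculation assumes one test per measure and jointly normal test statistics. The correlations are illustrative, so the range is the result and no single value in it should be quoted as the trial's error rate.

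This should be corrected, but it does not threaten the primary analysis.

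**What to change.** 1. **Data analysis.** Replace the per-outcome threshold with a statement that ICU length of stay alone is tested at two-sided .05 and decides effectiveness. All secondary outcomes are supportive or exploratory, reported as estimates with the 95% confidence intervals already planned and without a claim of effectiveness.
2. **Abstract.** Reword the purpose to match the last paragraph of the Introduction: effectiveness on ICU stay, with the other outcomes listed as secondary.
3. **Only if confirmatory claims on a few secondaries are wanted.** Name them, and test them after ICU stay by Holm or in a fixed order. Before FSS can be one of them, its definition must be reconciled. The sample size section uses a yes/no endpoint (FSS = 35) at hospital discharge, while the Intervention outcomes section measures FSS at 28 days or ICU discharge.

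The cost is wording only, with no added patients, visits or data. The downside is that a secondary result can no longer support an effectiveness claim by itself.
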